# **2 BACKGROUND AND RATIONALE**

**Background:** Dramatic advances in technology are being adopted into clinical rehabilitation practice at a rapid pace. Robotic exoskeletons (wearable robots to enhance overground mobility) are a potentially viable technology that can be used for gait training among those with acute spinal cord injury (SCI). Yet, foundational evidence to support exoskeleton use during the acute phase of recovery is lacking . While robotic exoskeleton technology is not yet mature enough to produce independent community ambulation,^1,2^ the technology has improved^3^ and may allow for enhanced SCI rehabilitation.^4^ Over the past 20 years robotic exoskeleton use has primarily been studied in people living with chronic SCI, with early evidence demonstrating that use improves gait, bone density, body composition, and specific cardiovascular parameters.^5^ One exciting, yet understudied, application of robotic exoskeletons in rehabilitation is the possibility of enhancing functional outcome by using the device during the acute recovery phase,^6^ when the central nervous system’s ability to reorganize itself by forming new neural connections, known as neuroplasticity, is greatest and changes in functional recovery most likely.^7^ Notably, more than half of expected recovery occurs in the first two months after SCI and subsequent improvement plateaus after 3 to 6 months.^8^ This critical period of neuroplasticity suggests that functional recovery may be greater using rehabilitation approaches that maximize the potential for generating neuroplasticity. Initial evidence of robotic exoskeleton use that our team at Baylor Scott & White Institute for Rehabilitation (BSWIR) has generated demonstrates that this technology may offer a better approach for gait training that yields improved functional outcomes over traditional gait training approaches. This study proposed in this application systematically builds upon our initial evidence examining the feasibility and effect of robotic gait training (RGT) during acute rehabilitation to improve walking recovery after SCI.

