**Eligibility Criteria**

Individuals (n = 128) between the ages of 16 – 85 years within 6 months post-incomplete SCI who are admitted to BSW and who meet criteria to use an EKSO robotic exoskeleton will be recruited to participate in this study. Subjects must meet Ekso robotic exoskeleton frame limitations unless per the discretion of the PI it is determined that subject’s weight and/or height being outside of this range does not interfere with the fit of the device. Patients will be screened at admission for initial eligibility and qualifying patients will be approached to participate. Patients will be evaluated by clinicians to determine if they meet the inclusion/exclusion criteria during their inpatient stay. If a patient is not initially appropriate for intervention due to medical reasons and later determined to appropriate during their stay, they may be approached to consent to participate. In a private setting, patients, and their caregivers if applicable, will be approached about the study and a study team member will briefly explain the study and answer any patient questions for clarification. Caregivers of minors will sign consent form and minors will be given an opportunity to assent to project. Inclusion/exclusion listed below.

| **Table 4. Eligibility Criteria** | |
| --- | --- |
| **Inclusion Criteria** | **Rationale** |
| 16-85 years of age | Broad range for generalizability; Our inpatient rehabilitation facility admits patients with SCI who are 16 years and older. Patients who are 16 and 17 years of age are likely to receive similar gait interventions as adults aged 18+ and able to meet manufacturer height and weight specifications of the Ekso robotic exoskeleton device. This is consistent with previously published exoskeleton research.^1^ 97% of patients at BSW were between 18-70 with average age of SCI admissions over the past 5 years being 56.0 ± 18.6 years. |
| All types of incomplete SCI (traumatic and non-traumatic) | Broad range for generalizability. In this study, we will include people with incomplete SCI regardless of presence of tetraplegia or paraplegia (~68% of all people with SCI)^15^ because of the greater potential for motor recovery. |
| Acute/Subacute phase of recovery | We will include patients with incomplete SCI admitted to BSW for inpatient rehabilitation within 6 months post-SCI (~88% of admissions over the past 5 years). |

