**Randomization**

Participants meeting the inclusion and exclusion criteria will be approached, screened, consented, and enrolled into the study. After obtaining informed consent, participants will be randomized to either the experimental (RGT) or UC control group using cluster randomization based on specific injury characteristic for stratified block.

The heterogeneity of the population in terms of injury severity is a concern given that these factors are expected to be important to walking recovery. To account for this, patients will be assigned to RGT or UC using 1:1 stratified blocks. Stratification will be based on specific injury characteristics (incomplete tetraplegia and incomplete paraplegia), and within each strata randomization blocks of size 6 will be used to ensure equal distribution between groups.

[figure not shown]

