# **6 STUDY MEASUREMENTS**

**Study Endpoints**

The following data will be collected through the medical record and patient interview at baseline assessment: age; age at injury; injury severity; gender; ethnicity; education level; pre-morbid history of mental illness; residence status; income; insurance type; vocation; and financial status. Level of impairment will be captured using the ASIA Impairment Scale (AIS) to determine injury severity after traumatic SCI by the physician at admission to BSW. The AIS is standard of care at BSW and will be extracted from the medical record. The following data will be collected through medical record and patient interview within one week of admission and discharge: *Gait speed via 10-Meter Walk Test, Spinal Cord Independence Measure (SCIM), Numerical Pain Rating Scale (NPRS), *Fatigue Severity Scale (FSS), Penn Spasm Frequency Scale (PSFS), Patient Health Questionnaire - 9 (PHQ-9), Life Satisfaction Questionnaire (LiSAT-9), Heart Rate (HR), Ratings of Perceived Exertion (RPE), and Number of Steps*. Primary and secondary outcomes for Aim 2 and dose parameters for Aim 3 are described in **Table 7.**

| **Table 7. Outcome Measures for Proposed Project and link to ICF** | | |
| --- | --- | --- |
| **Aim 2 Primary Outcome:** To examine the efficacy of RGT compared to usual care gait training (UC) | | |
| ****Walking Index for Spinal Cord Injury – II (WISCI-II)*** | Our primary outcome, the WISCI-II defines the physical limitation for gait secondary to impairment at the person level and indicates the ability of a person to walk after SCI.^103^ Intrarater and interrater reliability are excellent at 1.0 and 0.98 respectively.^104^ A change of one WISCI level can be considered clinically significant.^105^ | ICF domain = Activity |
| **Aim 2 Secondary Outcomes** | | |

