**Documentation of Data**

All participants will be given a subject identification number. This number will be used on all data collection forms and databases to ensure patient confidentiality. Hospital dates, onset of injury and demographic data will be extracted from patient report or medical record. Other data points can be collected from the participant directly onto the data collection form by the treating clinicians (or a member of the research team). Non-electronic data will be stored in a secured cabinet in the Research Office Suite. Data will then be entered into a secure database that only the study team will be able to access.

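### Time since injury, which the protocol itself treats as prognostic, is neither a stratum nor a named covariate; the cost is precision, not bias

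*Protocol*

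**What the plan says.** Protocol section 2 (Background and Rationale) gives a time course for recovery: "more than half of expected recovery occurs in the first two months after SCI and subsequent improvement plateaus after 3 to 6 months". Under Eligibility Criteria, patients are enrolled "within 6 months post-incomplete SCI who are admitted to BSW". Traumatic and non-traumatic incomplete injuries are both eligible.

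Under Randomization, "patients will be assigned to RGT or UC using 1:1 stratified blocks", with blocks of 6. The strata are defined as follows: "Stratification will be based on specific injury characteristics (incomplete tetraplegia and incomplete paraplegia". The reason given is heterogeneity in injury severity. Time since injury is not mentioned there.

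The baseline data listed in section 6 (Study Endpoints), and again in section 13 (Data Collection and Data Entry into Database), include "age; age at injury; injury severity; gender; ethnicity; education level" and several social and insurance items, but not time since injury. Section 13 (Documentation of Data) adds: "Hospital dates, onset of injury and demographic data will be extracted from patient report or medical record".

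Section 9 (Study Analysis Methods) says that every Aim 2 model adjusts for the admission score and for the demographic and impairment information listed in section B.1.i.D. No section of that number exists in this protocol.

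Both baseline lists describe the ASIA Impairment Scale (AIS) as used "to determine injury severity after traumatic SCI by the physician at admission to BSW". They then state that the AIS is standard of care and is extracted from the medical record.

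**The concern.** On the protocol's own account, where a patient stands on the recovery curve at entry should help to predict how far walking function improves by discharge. A window running to 6 months takes in patients from the steep part of that curve and patients well past it. The admission WISCI-II score removes some of this variation but probably not all: two patients at the same level, one at three weeks and one at five months, need not have the same expected gain. That last step is a statistical inference from the stated time course; the protocol does not say it.

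A prognostic factor that is measured but left out of the model stays in the residual variance of the primary outcome and of every secondary outcome. Any chance difference between arms in that factor also goes uncorrected. The onset and hospital dates are already being extracted, so this precision would be given up for nothing. The dead reference to section B.1.i.D makes matters worse, because a reader cannot tell which covariates the primary model will contain.

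**Working it through.** **1. The plan's own figure.** Inputs from section 9: effect size d = 0.5, 80% power, 5% level (two-sided assumed, as the sidedness is not stated). A two-sample t-test needs 63.8, that is 64 per arm, and 64 per arm gives 80.1% power. So 64 reproduces as the number before any allowance for attrition. The stated 10% allowance is a separate matter, but it means that about 58 per arm may be analysed (64 × 0.9 = 57.6), with power of 76.1%.

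**2. Gain from adjustment.** Let R² be the share of residual outcome variance that time since injury explains beyond the other covariates. The documents give no value; 5% to 20% is assumed. The standard error falls by 1 − √(1 − R²), and the effective effect size becomes 0.5/√(1 − R²).

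| R² (assumed) | Fall in SE | Effective d | Power, 64 per arm | Power, 58 per arm |
| --- | --- | --- | --- | --- |
| 0 | 0% | 0.500 | 80.1% | 76.1% |
| 0.05 | 2.5% | 0.513 | 82.1% | 78.2% |
| 0.10 | 5.1% | 0.527 | 84.1% | 80.4% |
| 0.20 | 10.6% | 0.559 | 88.1% | 84.7% |

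**3. Chance imbalance.** Suppose a share p of patients enters after two months; p is not stated and 0.3 to 0.5 is assumed. Treating allocation as unrelated to entry time, the SD of the between-arm difference in that share is √(2p(1 − p)/64), which is 0.081 at p = 0.3 and 0.088 at p = 0.5. The probability of a difference of 10 percentage points or more is 22% and 26% respectively. For 15 points or more it is 6% and 9%.

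**4. What such an imbalance does to the estimate.** Treating late entry as binary, the shift in SD units is imbalance × √R² / √(p(1 − p)). Over p = 0.3-0.5 and R² = 0.05-0.20, a 10-point imbalance shifts the estimate by 0.04 to 0.10 SD, and a 15-point imbalance by 0.07 to 0.15 SD. For comparison, the standard error is √(2/64) = 0.177 SD, and significance needs about 1.96 × 0.177 = 0.35 SD.

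**5. Bias and type I error.** In a simulation of stratified blocks of 6 (128 patients, 6,000 runs per scenario, R² of 5%, 15% and 30%), the analysis without time since injury rejected a true null in 5.7%, 5.2% and 5.1% of runs. Its mean estimates were within 0.01 of the true values of 0 and 0.5. Leaving out the covariate causes neither bias nor inflation of the type I error.

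**6. Whether age and age at injury can stand in.** If both are exact, their difference is time since injury. If both are in whole years (the protocol does not say) and time since injury is uniform over 0 to 0.5 years (assumed), the difference is 0 in 75% of patients and 1 in 25%. The variance of time since injury is 0.25/12 = 0.0208, that of the whole-year difference is 0.25 × 0.75 = 0.1875, and their covariance equals 0.0208. The squared correlation is therefore 0.0208/0.1875 = 11%. In the simulation, adjusting for this difference left power at about 81%, so almost none of the gain is recovered.

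**The case against.** Four objections have force.

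- **This is a randomised trial.** Allocation balances time since injury in expectation, and the models already adjust for the admission score. A reader might infer that early-phase and late-phase patients are compared without control, or that the result could be spurious. Steps 4 and 5 do not support that: type I error holds, the estimate is unbiased, and plausible imbalances move it by well under the 0.35 SD needed for significance.
- **The covariate list has not been seen.** The list in section 6 is of data collected and is not labelled as a model specification. It is only the apparent covariate list, and a separate analysis plan may name time since injury. This stands as a limit on the claim. But section 9 does fix the adjustment set by pointing to a section that is absent, and that is a defect of this document.
- **The size rests on assumed values.** Neither R² nor the late-entry share comes from the protocol, and at the low end the gain is two points of power. The 80% starting point is also for an unadjusted comparison, whereas the plan already adjusts for other variables. The background places the plateau after 3 to 6 months, so the 6-month ceiling sits at the end of that range, and how many patients would enter at plateau is not established.
- **The AIS wording.** A reader might infer that non-traumatic patients have no severity grade and would drop out of the adjusted models. The documents do not support that: injury severity is listed for all participants, and the AIS is called standard of care. The phrase is loose, no more.

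A reader might also want stratification by AIS, since severity is the reason given for stratifying. That would not address time since injury, and it is a trade-off, not the correction of an error.

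**Conclusion.** The point holds as a missed gain in precision joined to a dead cross-reference. The protocol describes a recovery course that makes time since injury prognostic, enrols across most of that course, collects the dates needed to measure it, and then gives it no role in stratification or in any covariate list that can be seen. The treatment comparison stays valid.

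Under an assumed 5-20% of residual variance explained, adjustment would raise power from about 80% to about 82-88% with 64 per arm, or from about 76% to about 78-85% with 58. The true gain could lie outside this range if time since injury explains more or less than assumed once the admission score and impairment are in the model.

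**What to change.** - **Covariates (section 9).** Replace the reference to section B.1.i.D with an explicit covariate list, and make the same replacement in the Aim 3 paragraph, which uses the same reference. Include days from injury or onset to admission, for example on the log scale, in every Aim 2 model, derived from the onset and hospital dates already extracted under section 13. Let it take the place of age at injury, which nearly duplicates age if both are recorded in whole years.
- **Wording clean-up (sections 6 and 13).** Delete the restriction to traumatic injury from the sentence on the AIS, so that the grade is clearly recorded for every enrolled patient.

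The cost is a wording amendment and one derived variable. No new data collection, no additional patients and no change to the randomisation strata are needed. The list should be fixed before outcomes by arm are examined.

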# **7 STUDY TERMINATION**

Each patient’s participation in the study will be terminated after completion of the study assessments. The end of study date is defined as the date when all data has been collected and statistically analyzed. However, the PI or the IRB may terminate the study at any time.

# **8 DATA QUALITY ASSURANCE**

PI and statistician will be responsible for ensuring the data is accurate. Data management functions conducted in the department will occur on a quarterly basis and will include data quality checks and verification, as well as internal edit and logic checks (e.g., out of range values, internal inconsistencies). Ten percent of charts will be audited for source document and data entry review. Cross tabulation checks using SAS will also be used. Data will be stored and backed-up periodically on the biostatistician’s space on the secure server. Descriptive statistics will be at calculated and included into quarterly reports to ensure the quality of data and progress of the study. In addition, a quality assurance coordinator independent of the study execution will conduct a quality assurance review at beginning of enrollment, midpoint and end of the study.

**Data Safety and Monitoring Board**

A 3-member external Data Safety and Monitoring Board (DSMB), including a Chairperson, will be established for FIRST. The DSMB will monitor the study and review quarterly the following: a) participant recruitment, accrual, retention, and withdrawal information; b) adverse events (AEs) and serious adverse events (SAEs); c) comparison of events that occur between treatment arms; d) individual events of particular concern; e) participant interview and/or performance status outcomes; f) other safety-supporting data requested by the DSMB; and g) summary of protocol violations, completeness and timeliness of study visit data, enrollment eligibility and ineligibility information, noncompliance, and unanticipated problems. None of these individuals on the DSMB will be directly involved in conducting this project or have a stake in its outcome. Funding for the DSMB is included in the budget and includes $300 per member, per year. Each DSMB member will meet at the beginning of the study with the PI and Co-Investigators to learn about the aims of the project, study design, and intervention.

The biostatistician will provide a data report four weeks prior to the DSMB teleconference meeting. Based on these Quarterly reviews, the DSMB may request specific responses from the PI. For example, the PI may be asked to provide additional plans for safety after a severe AE. The DSMB annual reports will enumerate the dates that the Committee meets, and its explicit procedures for monitoring patients’ safety and confidentiality, and data integrity, during the reporting interval. Actions taken by the IRB in response to AE reports will be immediately reported to the Project Officer and Research office.

# **9 STATISTICAL METHODS**

**Sample Size Considerations**

For the proposed project, 128 patients (64 per group) will be enrolled. All analysis will be performed using SAS 9.4 significance set at the 5% level. Sample size calculations were performed to determine the required sample size in each group based on detectable effect size. For 80% power with a 5% significance level we will need to obtain 64 participants in each group to detect a medium effect size of 0.5 and allow for ~10% attrition due to unplanned medical events, acute care transfers, and patient withdrawals. We anticipate minimal attrition as all treatments and outcomes will be assessed during the inpatient rehabilitation stay and we experienced 0% attrition during our feasibility study.

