**Study Analysis Methods**

**Aim 1 Analysis.** Our Aim 1 hypothesis is:

Hypothesis 1.1: *We will successfully engage key stakeholders in a community-based participatory research approach to develop the content and structure of the RGT program to accommodate current clinical practice guidelines and integrate emerging robotic exoskeleton technology.*

The Advisory Board of key stakeholders (patients, caregivers, clinicians, researchers, industry members) to review evidence-based literature, advise the research team on the unique aspects and goals of inpatient rehabilitation for people with SCI, review the RGT, and make recommendations for amendments to the RGT program based on our interim and final outcomes of the study over the funding period. The role of the advisory board is necessary to meet the needs of individuals post SCI based on previously demonstrated successful inclusion of RGT into clinical practice during inpatient rehabilitation and detected change in key outcome variables.

**Aim 2 Analysis.** Our Aim 2 hypotheses were:

*Hypothesis 2.1:* *Patients with incomplete SCI who receive RGT will have higher walking function (WISCI-II) at discharge compared to UC.*

*Hypothesis 2.2: Patients with incomplete SCI who receive RGT will have greater improvement of secondary outcomes (gait speed, daily function independence, pain, fatigue, spasm frequency, depressive symptoms, and quality of life) at discharge compared to UC.*

All analysis will be performed using SAS 9.4 with a significance level of 0.05. To determine if patients with incomplete SCI who receive RGT will have higher walking function than UC at discharge (Hypothesis 2.1), WISCI-II scores will be evaluated using a linear model. The distribution of WISCI-II scores will be assessed to determine if a general linear model will be utilized, or if a generalized linear model with an alternative distribution and link function, such as the gamma distribution with a log link, will be more appropriate. Similarly, all measures associated with the secondary outcomes in Hypothesis 2.2 (10MWT, SCIM, NPRS, FSS, PSFS, PHQ-9, LiSAT-9) will be evaluated with general or generalized linear models, as appropriate. A separate model will be run for each outcome. All models for both the primary and secondary outcomes will control for scores at admission as well as the patient’s demographic and impairment information listed in section B.1.i.D.

**Aim 3 Analysis:** Our Aim 3 hypotheses were:

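### The 64 per group is the no-attrition sample size: it contains no allowance for the stated 10% loss, after which unadjusted power is about 76%, not 80%

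*Protocol*

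**What the plan says.** Section 9 of the protocol, Sample Size Considerations, gives the only power justification in the document. It fixes enrolment: "128 patients (64 per group) will be enrolled". It then gives the reason, for 80% power at the 5% level: "we will need to obtain 64 participants in each group to detect a medium effect size of 0.5 and allow for ~10% attrition". The required number, the target effect and the allowance for loss thus stand in one sentence. The paragraph closes by expecting little loss, on the ground that "we experienced 0% attrition during our feasibility study".

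Two other parts of the protocol bear on the point. Study Analysis Methods, under Missing Data, leaves a missed assessment out of the model for that outcome; imputation appears only as a sensitivity analysis. For Aim 2, the same section specifies models that adjust for the admission score and for patient characteristics. No correlation or variance reduction from that adjustment enters the sample size statement.

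**The concern.** For these inputs, 64 per group is the familiar textbook answer for patients analysed, before any allowance for loss. The protocol uses it as the number enrolled and says that attrition is already covered. If so, the primary comparison reaches 80% power only when nobody is lost.

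Loss does reduce the analysed sample here. Outcome testing takes place only around admission and around discharge (section 5, Visit Windows), so a patient who leaves before discharge testing has no primary outcome and drops out of the primary model.

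At stake is how the trial is described and read. A funder, ethics board or monitoring board would conclude from the text that about 13 of the 128 patients could be lost with 80% power intact. A null result on the WISCI-II would be reported as coming from a trial with that power.

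**Working it through.** **Inputs, all from the protocol unless marked**

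- Enrolled: 64 per group, 128 in total (Sample Size Considerations).
- Allocation 1:1 (Randomization).
- Significance level 5%: "All analysis will be performed using SAS 9.4 significance set at the 5% level". The sidedness is not stated. Two-sided is assumed first, and one-sided is tested below because Hypothesis 2.1 is directional: RGT patients "will have higher walking function (WISCI-II) at discharge compared to UC".
- Standardised difference d = 0.5; power 80%; attrition 10%.

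**Step 1: reproduce the protocol's figure.** The normal approximation is n = 2(z₀.₉₇₅ + z₀.₈₀)²/d² = 2(1.960 + 0.842)²/0.25 = 62.8, so 63 per group. The exact calculation, with the noncentral t distribution, gives 63.77, so **64 per group**. Power at 64 is 80.1%. The stated number is thus reproduced by the two-sided t-test with attrition set to zero.

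**Step 2: apply the stated loss.** 64 × 0.9 = 57.6 per group, so 57 or 58; in total 128 × 0.9 = 115.2, about 115. Power comes from the noncentral t with noncentrality d·√(n/2) and 2n − 2 degrees of freedom:

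| Analysed per group | Noncentrality | Power, two-sided 5% | d detectable with 80% power |
| --- | --- | --- | --- |
| 64 | 2.83 | 80.1% | 0.50 |
| 58 | 2.69 | 76.1% | 0.525 |
| 57.6 | 2.68 | 75.8% | 0.527 |
| 57 | 2.67 | 75.4% | 0.529 |

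The normal approximation gives 76.1% to 76.8% at 57 to 58, so the choice of method hardly matters.

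**Step 3: what a 10% allowance would need.** 64/0.9 = 71.1, so 72 per group, 144 in total. That is 16 more than planned. With the normal approximation, 63/0.9 = 70 per group, 140 in total.

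**Step 4: does a one-sided test give 64?** At one-sided 5%, d = 0.5 and 80% power, the t-test needs 50.15, so 51 per group analysed. 51/0.9 = 56.7, so 57 enrolled. The normal approximation gives 50 analysed and 56 enrolled. Neither yields 64. At 57.6 analysed per group, one-sided power would be 84.7%.

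**Step 5: what could covariate adjustment recover?** In a normal linear model with one baseline covariate correlated ρ with the outcome, the effective difference is d/√(1 − ρ²). The protocol gives no ρ, so a range is shown, at 57.6 per group, two-sided:

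| ρ (assumed) | Power |
| --- | --- |
| 0 | 75.8% |
| 0.2 | 77.5% |
| 0.3 | 79.6% |
| 0.4 | 82.7% |
| 0.5 | 86.7% |

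Power returns to 80% at ρ = 0.31 (0.30 to 0.33 for 58 down to 57 per group).

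**The case against.** Four points can be made for the protocol.

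1. **Sidedness is not stated and the hypothesis is directional.** If the test is one-sided at 5%, about 85% power remains after 10% loss, and the power claim would be true. This stands as a condition on the conclusion. It does not explain the figure, because a one-sided calculation with 10% loss leads to 56 or 57 enrolled. Only the two-sided calculation without loss gives 64.
2. **The planned analysis is not an unadjusted t-test.** It adjusts for the admission score and other characteristics, so its power after 10% loss is unknown and may well exceed 80%. This also stands, and it means that 76% must be labelled as unadjusted. But the sample size statement does not invoke the adjustment and gives no correlation, so it cannot be the source of the claimed allowance.
3. **Real attrition may be small.** The protocol expects little and saw none in its feasibility study. With no loss, power is 80.1%; with 5% loss (60.8 per group) it is 78.1%. The practical shortfall may therefore be under 4 points. Low attrition would make an allowance unnecessary; it does not put one into the 64.
4. **The effect is small and the remedy is only wording.** True: a confidence interval will reflect whatever sample is achieved. Equally, a wrong figure in the only power statement is easily put right.

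Reading the 64 as completers is not open, because the same paragraph gives it as the number enrolled.

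**Conclusion.** The concern holds. The protocol's 64 per group is the sample size for zero loss, and the statement that it also covers about 10% attrition is wrong. On the two-sided, unadjusted reading, the only one that reproduces the stated number, a 10% loss costs a little over 4 percentage points of power (80.1% to about 76%) and moves the effect detectable with 80% power from 0.50 to about 0.53.

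The size depends on three things that the protocol leaves open or treats as favourable: a two-sided test, no gain from covariate adjustment, and a loss that actually reaches 10%. A change in any of them could bring power back to around 80% or above. None of them makes the sentence correct as written.

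**What to change.** Leave the sample size unchanged and correct the statement in Sample Size Considerations. Delete the clause that says 64 per group allows for attrition, and state the test as two-sided if that is what is intended. A suitable text:

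> We will enrol 128 patients (64 per group). With about 10% attrition, about 115 are expected to be analysed. In an unadjusted two-sided comparison at the 5% level this gives about 76% power for a standardised difference of 0.5, or 80% power for a difference of about 0.53. Without attrition, power for 0.5 is 80%.

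If the sponsor wants to rely on the planned adjustment, one conditional sentence can follow: in a linear model, adjustment for admission WISCI-II restores at least 80% power if the admission–discharge correlation is about 0.32 or more (about 87% at 0.5). It should be marked as an assumption, ideally supported by the sponsor's own earlier data. It applies to a normal linear model with one covariate and may not carry over if a gamma or other generalised model is chosen.

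The cost is one or two sentences and a slightly less favourable stated power. No patients, visits or analyses are added. The alternative, enrolling 72 per group so that the present claim becomes true, would cost 16 more patients and is not needed to correct the error.
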